### Sample size

We conducted a priori stochastic simulation and estimation to determine the appropriate sample size for our study. Assuming a 30% coefficient of variation (%CV) in drug exposure, we estimated that enrolling 40 participants per antibiotic would provide sufficient power to detect a 30% effect of HIV co-treatment on antibiotic exposure. In alignment with the ICH E9 guidelines on statistical principles for clinical trials and considering an anticipated 10–15% attrition rate due to study withdrawal and loss to follow-up, we increased the sample size by 10 participants per antibiotic. This adjustment results in a total of 50 participants per antibiotic, or 200 participants overall.

For intravenous antibiotics (ceftriaxone) and anti-TB drugs (rifampicin and isoniazid), we assumed a lower %CV of 25% in drug exposure. Based on this assumption and accounting for an anticipated 15% withdrawal rate, we estimate that a sample size of 25 participants will be sufficient to maintain the power needed to detect possible significant changes in drug exposure due to concomitant antiretroviral therapy.

Therefore, the total sample size for this study is 200 participants.

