### Safety assessment

A creatinine level will be measured in patients who undergo intensive pharmacokinetic blood draws, acutely ill in-patients and out-patients without a recent measurement. All other safety testing will be performed according to standard of care. Participants who are found to be pregnant during follow-up will not be excluded, however, pharmacokinetic data will be censored at that point.

Adverse event (AE) assessment and reporting will be conducted for participants undergoing dose adjustments for tuberculosis treatment. All observed or volunteered AEs, regardless of suspected causal relationship, will be reported. Adequate information will be obtained to evaluate the causality and severity of the AE using the Naranjo score and Division of AIDS (DAIDS) table respectively. Following adverse events, follow-up will be conducted until the event or its sequelae resolve or stabilize. Participants who suffer harm will be managed by the study which has provided trial insurance for those receiving dose adjustment.

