### Statistical analysis

**
*Analysis of data on antimicrobial drugs: sparse pharmacokinetic data*
**

Sparse pharmacokinetic data for antimicrobials will be analysed as medians with standard deviations. We assess for the effect of covariates like age, sex, body-mass index, CD4 cell counts on drug concentrations

**
*Analysis of data on antimicrobial drugs: intensive pharmacokinetic data*
**

Non-linear mixed-effects models will be used to calculate the pharmacokinetic parameters of the drugs and this will include the maximum plasma concentration (Cmax), time to maximum plasma concentration (Tmax), and area under the plasma concentration-time curve (AUC). We will also explore the effects of covariates like age, sex, concomitant medications, and body-mass index on the pharmacokinetic parameters.

**
*Pharmacodynamic parameters*
**

We will use pharmacokinetic and pharmacodynamic models to assess the effect of the pharmacokinetic parameters on clinical response. For sparse pharmacokinetic data, we will use drug concentrations as a covariate in the linear regression models predicting clinical response. Clinical response will be defined as either clinical cure (resolution of symptoms) or clinical failure (lack of improvement in signs and symptoms of infection or recurrence of signs/symptoms of infection after initial improvement or death considered at least possibly due to the infection.

**
*Analysis of data on anti-tuberculosis drugs*
**

For participants on anti-tuberculosis drugs, we will evaluate whether dose adjustment leads to the achievement of therapeutic targets.

As an exploratory objective, using Kaplan Meier survival analysis, time to sputum culture negativity will be compared for those who received dose adjustment and those who did not receive dose adjustment within this study. We will also utilize the SOUTH dataset where drug concentrations of rifampicin and isoniazid were measured (without dose adjustment), where 78% and 84% of participants had rifampicin and isoniazid concentrations below the therapeutic targets respectively.

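### The exploratory culture-conversion comparison of dose-adjusted and unadjusted TB participants is confounded by drug level, with an expected unadjusted group of 4 at most, and attainment has no unchanged-dose reference

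*Protocol article*

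**What the plan says.** All references are to the protocol article.

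- **Sample size.** For ceftriaxone and the anti-TB drugs, "we estimate that a sample size of 25 participants will be sufficient to maintain the power". The calculation concerns drug exposure ("we assumed a lower %CV of 25% in drug exposure"), not culture conversion.
- **Participants on anti-tuberculosis treatment.** Levels are measured after two weeks of treatment. Anyone below target on rifampicin, isoniazid or both has the dose of the low drug raised, and levels are measured again two weeks later. Allocation is not randomised.
- **Statistical analysis, exploratory.** Time to sputum culture negativity "will be compared for those who received dose adjustment and those who did not receive dose adjustment within this study", by Kaplan-Meier. The SOUTH dataset, which had no dose adjustment, will also be used; it is described as one "where 78% and 84% of participants had rifampicin and isoniazid concentrations below the therapeutic targets respectively". How it will be used is not stated.
- **Statistical analysis, attainment.** One sentence: "we will evaluate whether dose adjustment leads to the achievement of therapeutic targets". No method or comparator is named.
- **Introduction.** Sub-therapeutic rifampicin and isoniazid levels in SOUTH were associated with slower sputum conversion.

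**The concern.** The escalation rule decides who falls in which Kaplan-Meier group, and it works on drug level alone. Unadjusted means both drugs at target after two weeks; adjusted means at least one drug low. The article itself reports that low levels go with slower conversion. The comparison therefore sets participants with a known reason to convert late against those without one. A useful dose adjustment could appear useless or harmful, and more participants would not remove that bias.

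The SOUTH rates quoted beside the comparison also imply that almost nobody will be unadjusted, so even a descriptive curve for that group would carry very little information.

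The attainment question has a related weakness. Participants are selected for escalation because a measurement at one visit was low, and all of them are escalated. Some would be above target at the next visit through ordinary within-person variation. Nothing observed within the study separates that share from the effect of the extra dose, yet the wording is causal.

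**Working it through.** **1. Size of the TB group.** Three oral antibiotics at 50, ceftriaxone at 25 and TB at 25 give 3 × 50 + 25 + 25 = 200, the stated total. This supports reading the TB group as 25. The 25 comes from a simulation whose model, alpha and power are not given, so it cannot be formally reproduced. A simple two-group check is close: a 30% effect (stated for the 40-per-antibiotic calculation), CV 25%, and assumed two-sided 5% alpha and 80% power give 11 per group. Then 22 / 0.85 = 25.9, or 26. After "accounting for an anticipated 15% withdrawal rate", 25 × 0.85 ≈ 21 remain.

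**2. Expected number unadjusted.** At-target rates from SOUTH are 1 − 0.78 = 0.22 (rifampicin) and 1 − 0.84 = 0.16 (isoniazid). Being unadjusted requires both.

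- Upper bound on the probability: min(0.22, 0.16) = 0.16.
- If the drugs are independent: 0.22 × 0.16 = 0.0352.
- Lower bound: max(0, 0.22 + 0.16 − 1) = 0.

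| TB participants | Upper bound | Independent |
|---|---|---|
| 25 | 4.0 | 0.9 |
| 21 (after withdrawal) | 3.4 | 0.7 |
| 50 (if the TB group were that large) | 8.0 | 1.8 |

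These are expected counts. At 16% of 25, the 95% binomial range is 1 to 8, and the chance of 4 or fewer is 63%. Under independence, the chance of no unadjusted participant is (1 − 0.0352)^25 = 41%. If AUC served as a further trigger for escalation, the unadjusted group could only shrink.

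**3. Precision of the comparison.** The article claims no power here, so this is only a guide. Take the favourable case of 4 versus 21 with all 25 converting (an assumption). The standard error of the log hazard ratio is 1 / √(25 × 0.16 × 0.84) = 0.55. Power at two-sided 5% is about 11%, 25% and 52% for hazard ratios of 1.5, 2 and 3, and 80% power needs a ratio of about 4.6. The formula is a large-sample one and is unreliable with so few events in one group.

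**4. Direction of the bias.** The escalation rule makes a low level the condition for being adjusted. The Introduction ties a low level to delayed conversion. Together they predict slower conversion in the adjusted group before any effect of the extra dose is counted.

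**5. Attainment with no dose change.** Let p be the proportion below target and z = Φ⁻¹(p). Assume that log concentrations at the two visits are bivariate normal with the same distribution and correlation ρ. Among those low at the first draw, the share at target at the second with an unchanged dose is 1 − Φ₂(z, z; ρ) / p. The article gives no ρ, so a range is shown.

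| ρ (assumed) | Rifampicin, p = 0.78 | Isoniazid, p = 0.84 |
|---|---|---|
| 0.9 | 6.8% | 5.2% |
| 0.7 | 11.8% | 8.9% |
| 0.5 | 15.4% | 11.5% |
| 0.3 | 18.3% | 13.6% |

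The effect is modest but always runs towards showing benefit.

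**The case against.** **Status.** The Kaplan-Meier comparison is labelled exploratory, and Objective 2 is about reaching therapeutic targets, not culture conversion. A reader might infer that the flawed comparison undermines Objective 2; it does not. But the label does not make a contrast biased by its own group definition informative.

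**SOUTH is already planned.** This stands. SOUTH gives an external unadjusted group, most of it below target, so it would be wrong to say that the plan has no usable comparator. What the article fixes badly is the within-study contrast.

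**The count of 4 is soft.** This stands in part. It is a ceiling on an expectation. The Abstract can also be read as saying that only some TB participants have TDM, which would enlarge the unadjusted group; the treatment section reads as TDM for all. The confounding by level among monitored participants remains either way. The article also says that those who reach target return to the earlier dose, which blurs who counts as adjusted; these passages need reconciling.

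**Regression to the mean is not shown to be ignored.** This stands. No before-after analysis is stated, and the attainment method may be in a document not shown. What remains follows from the design: no sub-target participant stays on the same dose for re-measurement.

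**Timing.** A reader might infer that conversions before adjustment are credited to the adjusted group. The article gives no time origin, and all monitored participants are classified at the same week-2 draw, so both groups share the earlier period. That would mainly dilute a difference, not favour one group.

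**Adverse events.** A reader might infer from "Adverse event (AE) assessment and reporting will be conducted for participants undergoing dose adjustments for tuberculosis treatment" that the adverse-reaction outcome lacks a comparator. The sentence does not exclude others, the outcome list carries no such restriction, and no comparison of adverse events between the groups is planned.

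**Conclusion.** The concern holds for two things.

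First, the exploratory adjusted-versus-unadjusted comparison is confounded by design, in a direction that would mask a benefit. Its unadjusted group is expected to number at most 4 of 25, or about 1 if the drugs are independent. The count assumes a TB group of 25, TDM in all of them, and SOUTH rates that carry over. The confounding does not depend on the count.

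Second, causal wording about attainment is not identified from repeat levels alone. About 7–18% of low rifampicin and 5–14% of low isoniazid values would reach target unaided, on an assumed correlation of 0.9 to 0.3 and the bivariate normal model.

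The documents do not support going further: not to a failure of Objective 2 as a whole, a timing bias favouring the adjusted group, or a defect in adverse-event comparison.

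**What to change.** 1. Report the within-study adjusted and unadjusted culture curves descriptively only, without a test or effect estimate, or drop them.
2. Make the exploratory comparison one of adjusted participants against SOUTH participants with sub-target concentrations. Start both at a week-2 landmark among those still culture-positive, and adjust for baseline factors and drug level. Label it historical and exploratory. Confirm first that the timing of drug levels and cultures in SOUTH allows this; the article shows that SOUTH had both measures but not when.
3. For attainment, fit one model to both TDM visits with between-occasion variability. Report observed attainment beside the attainment the model predicts had the dose not changed, and word the conclusion accordingly.
4. State whether all TB participants have TDM, and how participants who return to their earlier dose are classified.

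The cost is a change of analysis wording and some extra modelling on data already planned, with no added participants or samples. The SOUTH comparison remains non-concurrent, and the prediction in step 3 rests on the model's estimate of within-person variability, which will be imprecise with about 21 to 25 people.

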## Protocol

### Study objectives

1. To determine the concentrations of selected antimicrobial agents in people living with HIV requiring antimicrobial therapy.2. To assess the utility of therapeutic drug monitoring in achieving therapeutic targets for people living with HIV receiving rifampicin and isoniazid for treatment of tuberculosis.3. To develop and validate a population pharmacokinetic-pharmacodynamic model for use during therapeutic drug monitoring for selected antibiotics used among PLWH

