### Participants on anti-tuberculosis treatment

The current tuberculosis (TB) treatment involves fixed dose combinations based on weight bands, including an intensive phase of rifampicin, isoniazid, ethambutol, and pyrazinamide (RHEZ) for 2 months, followed by a continuation phase of isoniazid and rifampicin (HR) for 4 months. Dosing is determined by weight bands, with 3, 4, or 5 tablets of RHZE or HR depending on weight (<55, 55–69, ≥70 respectively). Each tablet contains 150 mg of rifampicin and 75 mg of isoniazid for both combinations. Fixed dose combinations in the intensive phase include concomitant pyrazinamide and ethambutol.

Serum rifampicin and isoniazid concentrations (C2hr, C4hr, C6hr) will be measured in participants when fasting, and following directly observed therapy, after two weeks of treatment (First TDM). Results of blood concentrations will be received within 24–48 hours and assessed to determine if the C
_max_ and AUC is within the therapeutic targets. Sub-therapeutic C
_max_ concentrations are considered less than 8mg/L and 3mg/L for rifampicin and isoniazid, respectively. AUCs for rifampicin and Isoniazid will also be considered and compared with existing published therapeutic ranges
^
22
^. Participants found to have subtherapeutic drug exposures will have dose escalation and be asked to take one additional pill of the drug that did not achieve therapeutic target concentrations (rifampicin, isoniazid or both) (
Table 3). A second blood draw for measurement of drug concentrations will be performed after another two weeks (Second TDM) and dose adjustment performed again based on the guidance in
Table 3, if concentrations are still below the target. (
Figure 1)

**Table 3. T3:** Dose adjustment table for isoniazid and rifampicin in patients with HIV.

Weight band	Normal drug levels	Sub-target INH <3mg/dl Normal RIF	Normal INH Sub-target RIF <8mg/dl	Sub-target INH <3mg/dl and Sub-target RIF <8mg/dl
<55kg	Continue INH 225 mg and RIF 450 mg (3 FDCs)	Give an additional INH tablet equivalent to: INH 300 mg	Give an additional rifampicin tablet equivalent to 600 mg dose	Give additional rifampicin and isoniazid tablets or FDCs equivalent to 300 mg INH and 600 mg rifampicin

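### The main TB analysis has no comparator, so higher target attainment by the second TDM cannot be separated from the same dose step given without monitoring, or from regression to the mean

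*Protocol article*

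**What the plan says.** Study objectives, objective 2: "To assess the utility of therapeutic drug monitoring in achieving therapeutic targets" in people with HIV taking rifampicin and isoniazid for tuberculosis.

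Participants on anti-tuberculosis treatment: concentrations are measured after two weeks of treatment. Sub-therapeutic Cmax "concentrations are considered less than 8mg/L and 3mg/L for rifampicin and isoniazid, respectively"; AUC is also considered. "Participants found to have subtherapeutic drug exposures will have dose escalation and be asked to take one additional pill" of whichever drug fell short, with the amounts in Table 3. A second TDM follows two weeks later and can lead to another adjustment. After that come extra draws to look at absorption, a possible further tablet at the study team's discretion, and a return to the previous dose for those who reach target.

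Statistical analysis, anti-tuberculosis drugs: "we will evaluate whether dose adjustment leads to the achievement of therapeutic targets". An exploratory Kaplan-Meier analysis compares time to culture negativity between adjusted and unadjusted participants. The SOUTH dataset, which had no dose adjustment, will also be used. It is described as one "where 78% and 84% of participants had rifampicin and isoniazid concentrations below the therapeutic targets respectively".

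**The concern.** The objective is about monitoring, but the analysis sentence is about the dose change that follows it. The two come close only if monitoring sorts participants into groups that are treated differently. On the protocol's own reference figures it would hardly do so at the first step, because nearly everyone is moved up on at least one drug. A before/after rise would then be expected whether monitoring is useful or the starting dose is simply low for most people.

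The participants who are escalated are also chosen because one reading was low. Some would read higher at the next draw with no change in dose.

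The Discussion says the data will inform clinicians about the practicability of TDM and the utility of adjusting doses after it. A rise in attainment could therefore be reported as evidence for monitoring that the stated analysis does not supply.

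**Working it through.** **Group size.** Sample size gives 25 participants and Study design gives 50 for each of three oral antibiotics. Reading 25 as applying to ceftriaxone and to the TB group separately, 3 × 50 + 25 + 25 = 200, which reproduces the stated total.

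**Share escalated at the first TDM.** The protocol states no such figure. It follows from 78% (rifampicin) and 84% (isoniazid) below target:

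- full overlap: max(0.78, 0.84) = 0.84, or 21 of 25
- independence: 1 − 0.22 × 0.16 = 0.965, or 24.1 of 25
- least overlap: min(1, 0.78 + 0.84) = 1, or 25 of 25

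So 0 to 4 of 25 are not escalated on either drug. Those low on exactly one drug run from 0.78 + 0.84 − 2 × 0.78 = 6% to 0.78 + 0.84 − 2 × 0.62 = 38%.

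**Comparison with an unmonitored step.** At the second TDM, a participant who was low on a drug has received the dose of that drug they would have had if everyone had been stepped up untested. Attainment in that group is the same under both rules, with no modelling needed. Up to that point monitoring differs only in sparing those already at target: 0.22 × 25 = 5.5 for rifampicin and 0.16 × 25 = 4 for isoniazid.

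**Regression to the mean.** Assume log Cmax is bivariate normal over the two draws, with 30% of log-variance within person (correlation ρ = 0.7; not from the document). Let p be the share below target at the first draw and z = Φ⁻¹(p). With no dose change, the share of low participants reaching target at the second draw is 1 − Φ₂(z, z; ρ)/p.

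- rifampicin: z = 0.772, 1 − 0.688/0.78 = 11.8%
- isoniazid: z = 0.994, 1 − 0.765/0.84 = 8.9%

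For ρ from 0.3 to 0.9 the ranges are 18% to 7% and 14% to 5%.

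**Attainment under three rules.** Sample size assumes a 25% CV for these drugs, so the log SD is s = √ln(1 + 0.25²) = 0.246. Table 3 gives dose ratios k of 600/450 = 1.33, 750/600 = 1.25 and 900/750 = 1.20, and the isoniazid ratios are the same. Assume concentration is proportional to dose, and let c = z − ln(k)/s.

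- no change: 1 − p
- step for all: 1 − Φ(c)
- TDM rule: [p − Φ₂(z, c; ρ)] + [1 − 2p + Φ₂(z, z; ρ)]

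Example, rifampicin with k = 1.25: c = 0.772 − 0.223/0.246 = −0.134. Step for all gives 55%; the TDM rule gives 0.352 + 0.128 = 48%.

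| Drug | Step | No change | TDM rule | Step for all | Initially low, either rule |
|---|---|---|---|---|---|
| Rifampicin | +20% | 22% | 42% | 49% | 38% |
| Rifampicin | +25% | 22% | 48% | 55% | 45% |
| Rifampicin | +33% | 22% | 57% | 65% | 57% |
| Isoniazid | +20% | 16% | 35% | 40% | 31% |
| Isoniazid | +25% | 16% | 41% | 46% | 38% |
| Isoniazid | +33% | 16% | 50% | 57% | 50% |

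The gain over no change is about 20 to 35 points for rifampicin and 19 to 34 for isoniazid. Attainment at the second TDM is nevertheless no higher under the TDM rule than under the unmonitored step. Attainment here means exceeding the lower threshold only; the Introduction gives isoniazid a desired range of 3 to 6 mg/L.

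**The case against.** The strongest reply is that TDM means measuring and then adjusting, so it can act only through dose. A gain that comes through the tablet is its mechanism and not an error. Objective 2 names no unmonitored increase as comparator. The natural reference is standard dosing without TDM, and SOUTH is an unadjusted dataset that can serve for it. This stands. A reader might infer that the study cannot show that monitoring adds anything, and the documents do not support that: a non-randomised comparison with standard dosing is open to it.

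A reader might also describe the intervention as one tablet more for nearly everyone. That goes too far as well. Escalation is drug-specific, at 78% and 84% per drug; only the share escalated on either drug reaches 84% to 100%. The second TDM, the absorption draws, the discretionary tablet and the return to the previous dose are all driven by monitoring, and a single untested step reproduces none of them. Sparing participants an increase is itself a contribution.

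The escalation share is a forecast. The article does not say that SOUTH used the same thresholds, sampling times or population. How SOUTH enters the analysis may be set out in the full protocol or SAP, so its absence here is not a fault.

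What the reply does not remove is the gap at the first step. SOUTH had no adjustment, so it cannot separate measuring from a higher dose. The Kaplan-Meier analysis is exploratory, concerns culture conversion rather than attainment, and would have 0 to 4 unadjusted participants. Neither corrects for selection on a low reading.

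**Conclusion.** The point holds in limited form. As stated, the main TB analysis is an uncontrolled reading of attainment after adjustment. It can support a statement about TDM with adjustment against standard dosing, non-randomised, if SOUTH is used that way. It cannot support a claim that monitoring improves attainment over the same step given untested, and the before/after change is not a clean estimate of the tablet's effect either.

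The size rests on SOUTH's rates carrying over: 84% to 100% escalated on at least one drug. Second-TDM attainment would be 42% to 57% (rifampicin) and 35% to 50% (isoniazid) under the TDM rule, against 49% to 65% and 40% to 57% if all received the step. These are illustrations. They rest on lognormal Cmax, dose-proportional concentrations and the assumed 30% within-person share, together with the document's CV and Table 3 ratios. The identity in initially low participants needs none of these. No dose or dosing rule is judged here.

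**What to change.** In the Statistical analysis section for anti-tuberculosis drugs:

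1. Report the before/after change in attainment for each drug as descriptive, and attribute it neither to TDM nor to the extra tablet.
2. Add model-predicted attainment per drug under three rules: no change, the same step without monitoring (an analytic reference only, not a treatment proposal), and the TDM rule as applied. Use the week 2 and week 4 concentrations, the recorded doses and a population pharmacokinetic model that includes within-person variability, so that regression to the mean is accounted for. SOUTH may inform the no-change rule.
3. Give intervals, the number spared an increase on each drug, and any gain at later TDM steps.
4. State the Objective 2 conclusion as TDM plus adjustment versus standard dosing, labelled non-randomised. Claim a benefit of monitoring itself only from the contrast between the TDM rule and the unmonitored step.

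This needs no new participants, samples or change in treatment; the cost is wording and modelling time. The headline TDM effect becomes smaller, and the added estimates will be imprecise and partly model-dependent with about 25 participants.
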